**Fig. 2 Fig2:**
[figure not shown]
Schedule of enrollment, interventions, and assessments. ICF, informed consent form; ECG, electrocardiogram; TSAT, transferrin saturation; SF, serum ferritin; HsCRP, hypersensitive C-reactive protein; Hct, hematocrit; Hb, hemoglobin

### Eligibility criteria

The target population in this study are participants undergoing maintenance hemodialysis and who can meet the following eligibility criteria.

#### Inclusion criteria

Participants must meet all the following criteria to be enrolled in the clinical trial [12]:
Age 18–75, either genderMaintenance hemodialysis participants (≥3 months), dialysis frequency 3 times/weekHemoglobin concentration ≥110g/L and <130g/LTransferrin saturation >20% and <50%Serum ferritin >200μg/L and <500μg/LUsed biosimilar epoetin and iron at least 12 weeks before enrollmentSigned ICF voluntarily

#### Exclusion criteria

Participants who meet any of the following criteria will not be eligible to participate in this clinical trial:
Iron allergy, allergic history, or intolerance to test drugsHaving erythrocyte aplastic anemia, other hematopoietic and hemolytic diseasesAcute or chronic bleedingSerum albumin < 35g/LHypersensitive C-reactive protein >10 mg/LSevere secondary hyperparathyroidism (iPTH ≥800 pg/mL)Severe cardiac dysfunction (NYHA score > 3) and poor control of hypertension (systolic blood pressure ≥ 180 mmHg or diastolic blood pressure ≥ 100 mmHg)Severe liver disease (ALT, AST, and TBIL ≥ 2 times the upper limit of normal) or hepatitis B surface antigen positive, or hepatitis C antibody positiveMalignant tumorSevere bacterial or viral infection that occurred in the last 1 month, prior to signing the consentHistory of blood transfusion in the last 1 monthAdmitted to a hospital or planned a kidney transplant within the next 24 weeksPregnant or breastfeeding womanLife expectancy less than 12 monthsParticipating or has participated in clinical trials of other drugs within the last 3 monthsGastric or duodenal ulcers or ulcerative colitisHistory of chronic alcohol abuse, substance abuse. The presence of conditions that the investigator believes may affect participants’ compliance or test results

### Randomization and allocation

A central randomization method will be adopted in this study, and the principles of open and randomized control will be followed. All eligible participants will be randomly divided into an experimental group or the control group in a ratio of 1:1. An interactive web response system (IWRS) of the electronic data acquisition system (EDC) will be used to allocate and manage the random number, and the experimental drug (iron polysaccharide complex or iron sucrose injection) will be distributed according to the group corresponding to the random number. All information, including failure and success of participants screening, will be recorded, registered, and managed in the EDC system.

### Intervention

#### Experimental group

Iron polysaccharide complex (150mg) will be taken orally, 2 capsules per day, for 24 weeks. Participants will be treated with biosimilar epoetin (no need to dilute) intravenously with a single dose of 10,000U once a week during the maintenance period. At the same time, biosimilar epoetin dosage will be adjusted according to the measured hemoglobin concentration, as follows [7].
Discontinue biosimilar epoetin if Hb ≥ 130 g/L. Hb levels will be checked once every 2 weeks. If the Hb level drops to 110–130 g/L, the original biosimilar epoetin dose will be reduced by 25% or extended to once in 10 days for continuation.If Hb < 110 g/L, TSAT, and SF are met, biosimilar epoetin will be administered as a single dose of 10,000U at least three times, every 2 weeks. Also, the Hb values of participants will be evaluated once every 2 weeks. The maximum dose of biosimilar epoetin will be 10,000U twice a week. If TSAT and SF fail to meet the standard, the iron deficiency will be corrected first, and the biosimilar epoetin treatment regimen will be adjusted once TSAT and SF are within the desired range.

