**Methods:**

This randomized controlled trial uses an open-label, parallel group design, where the efficacy and safety of maintenance hemodialysis (MHD) participants is evaluated. The experimental group is assigned erythropoietins and iron polysaccharide complex (two capsules each time, bid), and the control group is assigned erythropoietin and sucrose iron (100mg, 2w) injection. Participants (aged 18–75 years) undergoing maintenance hemodialysis were considered for screening. Inclusion criteria included hemoglobin (Hb) ≥110g/L and < 130g/L, transferrin saturation (TSAT) > 20% and < 50%, and serum ferritin (SF) > 200μg/L and < 500μg/L. Exclusion criteria included acute or chronic bleeding, serum albumin < 35g/L, hypersensitive C-reactive protein (HsCRP) > 10 mg/L, and severe secondary hyperparathyroidism (iPTH ≥ 800 pg/mL). Full inclusion and exclusion criteria are described in the “Methods” section. The primary endpoint is TSAT of the participants at week 12. Secondary endpoints include Hb, SF, hematocrit (Hct), HsCRP, pharmacoeconomic evaluation, drug costs, quality of life, and indicators of oxidative stress. The treatment will last for 24 weeks with a follow-up visit at baseline (within 7 days prior to initial treatment) and weeks 4, 8, 12, 16, 20, and 24 after initial treatment. This clinical research includes 9 hemodialysis centers in mainland China and plans to enroll 186 participants.

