### Sample size

This clinical trial set has a non-inferiority threshold of 7 (%) and a variance of 11 (%) for the positive control group. We predict a 2% real difference between the tested drug and positive control in transferrin saturation. The unilateral significance level is 2.5%, with an assurance of 80%. In the case of a 1:1 sample size between the control group and the experimental group, a total of 154 samples will be collected (77 of which will be in the control group and the experimental group, respectively). Considering a 20% drop-out rate, the actual planned inclusion number will be 186 cases.

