### Dose adjustment within the next 24 weeks

If TSAT < 20% occurs during the test, the dosage of the iron agent will be adjusted as follows.
Iron polysaccharide complex: The iron polysaccharide complex prescription will be adjusted from one capsule daily to two capsules twice dailyIron sucrose injection: the prescription of iron sucrose injection will be adjusted from “100 mg/time, intravenous drop, once every two weeks” to “100 mg/time, once a week.” If SF ≥ 500 μg/L and/or TSAT ≥ 50% after the above treatment, iron supplementation therapy will be stopped and SF and TSAT will be reevaluated twice a week. If SF < 200 μg/L and/or TSAT < 20%, or SF 200–500 mg/L and/or TSAT 20%–50% are found twice consecutively, iron supplementation therapy will be restarted. Iron supplementation therapy is iron sucrose injection 100 mg/time, intravenous drip, once a week

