### Endpoints

#### Primary endpoint

TSAT will be measured at 12 weeks after baseline treatment.

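### The oral iron dose is given as four, two or one capsules a day in different sections, and on the abstract's dose the escalation step changes nothing

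*Protocol article*

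**What the plan says.** Three sections of the protocol article describe the dose of iron polysaccharide complex in the experimental arm.

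- **Abstract, Methods:** participants are assigned "iron polysaccharide complex (two capsules each time, bid"), that is, two capsules at each of two daily intakes.
- **Intervention, Experimental group:** "Iron polysaccharide complex (150mg) will be taken orally, 2 capsules per day, for 24 weeks".
- **Dose adjustment within the next 24 weeks:** the rule opens with "If TSAT < 20% occurs during the test, the dosage of the iron agent will be adjusted as follows". For the oral drug, the prescription then goes from a single capsule a day to two capsules at each of two daily intakes.

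The control regimen agrees with itself. The Abstract gives "sucrose iron (100mg, 2w) injection", the Control group section gives 100 mg once every two weeks, and the dose-adjustment section moves it from "100 mg/time, intravenous drop, once every two weeks” to “100 mg/time, once a week".

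The primary endpoint is fixed by "TSAT will be measured at 12 weeks after baseline treatment". The Sample size section sets a "non-inferiority threshold of 7 (%) and a variance of 11 (%) for the positive control group".

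**The concern.** All three statements are current text about the same arm, and they cannot be read as stages of one schedule. The only escalation rule starts from a dose that neither the Abstract nor the Intervention section prescribes, and it ends at the dose that the Abstract gives as the regular regimen.

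Four things depend on the dose:

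- **Primary comparison.** Iron dose is expected to act directly on TSAT at week 12. If the regimen is undetermined, a reader cannot tell which oral dose a non-inferiority conclusion supports.
- **Escalation and exit.** TSAT below 20% triggers escalation, and TSAT at or below 20% within two consecutive months is an exit criterion. If participants already take four capsules a day, the oral arm has no room to escalate before exit, while controls can double their dose. That would bear on retention and on the comparison between arms.
- **Drug cost.** This secondary endpoint includes iron supplementation.
- **Compliance and tolerability.** Good compliance, which the per-protocol set requires, needs a prescribed dose to be judged against. Gastrointestinal tolerability, a main reason given for using the product, has to be read against a known dose.

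**Working it through.** **Context: the plan's own sample size.** The inputs are in the Sample size section: margin 7, spread 11 (read as a standard deviation, although the text calls it a variance), assumed true difference 2, one-sided alpha 2.5%, power 80%. The distance to the margin is 7 − 2 = 5.

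Normal approximation: n per arm = 2 × 11² × (1.960 + 0.842)² / 5² ≈ 76. The noncentral t distribution gives power 0.795 at 76 per arm and 0.800 at 77, which matches the stated 77 per arm (154 in total). None of these inputs contains the capsule dose, so the dose conflict does not change this figure.

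**Step 1: starting dose.** Capsules per day = capsules per intake × intakes per day. The escalated dose is 2 × 2 = 4 a day, and the escalation factor is 4 divided by the starting dose. The last two columns are capsule totals at the unescalated dose over 84 days (12 weeks) and 168 days (24 weeks).

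| Section | Starting dose (capsules/day) | Escalation factor | Total by week 12 | Total by week 24 |
|---|---|---|---|---|
| Abstract | 2 × 2 = 4 | 4/4 = 1 (no change) | 336 | 672 |
| Intervention | 2 | 4/2 = 2 | 168 | 336 |
| Dose adjustment (implied) | 1 | 4/1 = 4 | 84 | 168 |

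The largest starting dose over the smallest is 4/1 = 4.

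**Step 2: comparison with control.** Going from 100 mg every two weeks to 100 mg weekly is a factor of 2. Only the Intervention section's dose gives the two arms the same escalation factor.

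**Step 3: milligrams (conditional).** The Intervention section does not say whether 150 mg is the content of one capsule or of the daily dose.

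- If it is per capsule, the three starting doses are 4 × 150 = 600, 2 × 150 = 300 and 1 × 150 = 150 mg a day.
- If it is the content of the two daily capsules together, each holds 75 mg and the doses are 300, 150 and 75 mg a day.

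The 1 : 2 : 4 ratio is the same on either reading.

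**The case against.** The best defence is that the three statements do not have equal standing. Only the Intervention section is an operative dosing instruction. The Abstract is a summary, and the single daily capsule appears only as the starting point of an escalation rule. On that view the intent can be recovered: two a day rising to four, which mirrors the doubling in the control arm. The single daily capsule would be a slip for one capsule twice daily, and the Abstract's dose may have been carried over from the escalated regimen. The trigger and the escalated dose are each stated once without conflict, so a site starting from either two or one a day could apply the rule.

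The defence adds that sites work from the full protocol, version 1.1, which is not shown. Recruitment is dated 1 April 2021 and the article appeared on 10 October 2021, so the article is unlikely to be what sites dose from.

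Much of this is fair. The one-a-day figure is implied rather than prescribed, two a day is the most plausible reading, and nothing shows that any centre dosed differently. The cost endpoint may also rest on actual use rather than nominal dose, and the per-protocol definition states no dose threshold.

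The contradiction remains. The plausible reading needs two of the three sections to be wrong, and nothing in the document says which. An article may leave detail to the full protocol, but here the dose is stated, and stated inconsistently.

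**Conclusion.** The concern holds. The test drug's starting dose is undetermined over a four-fold range, and the escalation rule starts from a dose that neither stated regimen uses. On the Abstract's dose, escalation does nothing while controls double.

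The capsule counts and ratios follow from the text alone. The milligram figures rest on an assumption about what 150 mg refers to. Different treatment across the nine centres is a possibility that the text allows, not something it shows. That two a day rising to four was intended is inference, and only the sponsor can confirm it.

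This should be corrected before the results are read, because the dose bears directly on week-12 TSAT and on drug cost. It is an internal inconsistency in the regimen; the margin, the test and the sample size are unaffected.

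**What to change.** State one starting dose and one escalated dose, each as capsules per intake and intakes per day, with the iron content per capsule. Use the same wording in the Abstract, the Experimental group section and the dose-adjustment section. If the intended regimen is one capsule twice daily rising to two capsules twice daily, the Abstract and the dose-adjustment starting point both need changing.

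Then check version 1.1 of the full protocol and the site instructions against the corrected text, and confirm that all nine centres have used that regimen. If any have not, report the doses given by centre alongside the primary result.

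Recording the prescribed dose at each visit would give compliance and cost a common denominator. It is a useful addition that the full protocol may already contain.

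The cost is a correction to the article and, if needed, a notice to sites. No new outcome data are required.

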### Setting and recruitment

A total of 186 subjects will participate in the study and will be recruited from 9 participating research centers (the hospital). Prior to recruitment, the investigator will carefully study the past condition, including but not limited to disease diagnosis and previous dialysis status of each participant. Researchers will fully consider the compliance of the participants within 24 weeks based on asking the participants. Informed consent forms (ICFs) will be obtained before collecting any participant data and participant information. After the participants sign the ICFs, the investigators will also sign the ICFs and record the informed consent process in the medical records. Hemodialysis participants eligible for inclusion in the trial will receive intravenous infusion (100mg total) of iron sucrose for 2 weeks after initial screening. If they still meet the inclusion criteria, they will be formally enrolled and started on medication. The treatment follow-up period of each participant is 24 weeks; the follow-up point of the screening and treatment period are shown in Fig. 2.

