#### Control group

One hundred milligrams of iron sucrose injection dissolved in 100 mL 0.9% sodium chloride solution will be intravenously administered at the end of dialysis once every 2 weeks for 24 weeks. During this period, participants will continue to receive intravenous biosimilar epoetin treatment in the same way as the experimental group. For the first intravenous infusion of iron sucrose injection, a small test dose will be performed. The test method refers to the drug instructions of iron sucrose injection, which are as follows.
Dosage: 1–2.5 mL (20–50 mg iron content) for adults. Children should be given 1 mL (iron content 20 mg) each time with body weight > 14 kg and given half of the daily dose (body weight kg × 1.5 mg/kg) each time with body weight < 14 kgCaution: cardiopulmonary resuscitation equipment should be available during the test. If no adverse reactions occur after 15 min of administration, the remaining administration can be continued

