#### Secondary endpoints

TSAT of participants’ changes between groups at 24 weeks of treatmentHb, SF, Hct, and HsCRP values of participants’ changes between groups at 0, 12, and 24 weeks of treatmentDrug costs for participants’ changes between groups at 24 weeks of treatment (including cumulative biosimilar epoetin dose and iron supplementation)Quality of life scale scores EQ5D-5L of participants’ changes between groups prior to treatment and at 24 weeks of treatment [12]Indicators of oxidative stress, including malondialdehyde (MDA), superoxide dismutase (SOD), and glutathione peroxidase (GSH-Px), will be measured in participants’ changes between groups at 0, 12, and 24 weeks of treatment [12]Cardiovascular events during the follow-up

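### The epoetin step for Hb below 110 g/L can be read as 5,000 U/week or as 15,000 to 20,000 U/week, and the text does not exclude either reading

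*Protocol article*

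**What the plan says.** The Experimental group section sets maintenance epoetin as given "intravenously with a single dose of 10,000U once a week during the maintenance period". Two Hb-driven adjustments follow.

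- **High Hb.** Epoetin stops at Hb of 130 g/L or more. Once Hb is back in range, "the original biosimilar epoetin dose will be reduced by 25% or extended to once in 10 days for continuation".
- **Low Hb.** Below 110 g/L, with TSAT and SF on target, "biosimilar epoetin will be administered as a single dose of 10,000U at least three times, every 2 weeks". Hb is evaluated every two weeks, and "The maximum dose of biosimilar epoetin will be 10,000U twice a week". If TSAT and SF are off target, iron deficiency is corrected before epoetin is changed.

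The Control group section carries the rules over: "participants will continue to receive intravenous biosimilar epoetin treatment in the same way as the experimental group". Under Secondary endpoints, 24-week drug costs are described as "including cumulative biosimilar epoetin dose and iron supplementation", and Hb is compared at 0, 12 and 24 weeks. Participants are "recruited from 9 participating research centers".

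**The concern.** The low-Hb sentence joins a dose, a minimum count and a two-week phrase without saying what the two weeks govern. They may be the spacing between single injections, with at least three given in all. They may instead be the window in which at least three injections are given. No other section of the article restates the step or settles the point.

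The readings move the dose in opposite directions from maintenance: one lowers epoetin in a participant whose Hb is already low, the other raises it. Inclusion requires Hb of at least 110 g/L, so the trigger lies directly below the entry limit, although the article gives no expected frequency of such episodes.

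Epoetin is a co-intervention in both arms. Its cumulative dose is a named part of the drug-cost endpoint, it acts on Hb, and cost-effectiveness is among the stated objectives. If sites read the step differently, those secondary outcomes carry variation that has nothing to do with the iron product. The wording also bears on participant safety, because it leaves unclear how much epoetin is given when Hb is low.

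**Working it through.** The article gives no weekly total for the low-Hb step, so there is no stated figure to reproduce. The inputs all come from the Experimental group section: 10,000 U per dose, maintenance once weekly, the low-Hb sentence, the restart rule, and the maximum of two doses a week.

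**Step 1. Weekly rates**

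- Maintenance: 1 × 10,000 = 10,000 U/week.
- Interval reading (one dose per two weeks): 10,000 / 2 = 5,000 U/week, or 0.5 × maintenance.
- Period reading, minimum (three doses per two weeks): 3 × 10,000 / 2 = 15,000 U/week, or 1.5 × maintenance.
- Stated maximum: 2 × 10,000 = 20,000 U/week, or 2 × maintenance.
- Ratio of the readings: 15,000 / 5,000 = 3.0 at the minimum, and 20,000 / 5,000 = 4.0 at the maximum.

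**Step 2. Comparison with the restart rule after high Hb**, if the original dose was 10,000 U/week

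- 25% reduction: 0.75 × 10,000 = 7,500 U/week.
- Ten-day spacing: 10,000 × 7 / 10 = 7,000 U/week.

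On the interval reading, a participant with low Hb receives less (5,000 U/week) than one resuming after high Hb (7,000 to 7,500 U/week).

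**Step 3. One episode.** Three two-weekly doses cover 3 × 2 = 6 weeks, so 6 weeks is the shortest episode that fits the interval reading. One such episode is assumed, with maintenance in the other 18 weeks (18 × 10,000 = 180,000 U).

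| | 6-week dose (U) | 24-week total (U) | Against 240,000 U |
|---|---|---|---|
| Interval reading | 6 × 5,000 = 30,000 | 210,000 | −12.5% |
| Constant maintenance | 6 × 10,000 = 60,000 | 240,000 | 0 |
| Period reading, minimum | 6 × 15,000 = 90,000 | 270,000 | +12.5% |
| Period reading, maximum | 6 × 20,000 = 120,000 | 300,000 | +25% |

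The three- to four-fold spread is therefore a rate within the episode. Over 24 weeks with one episode, the ratio is 270,000 / 210,000 = 1.29 to 300,000 / 210,000 = 1.43.

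**Step 4. Which reading the text favours.** For the period reading:

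- The maximum equals four doses per two weeks, so a minimum of three gives a coherent range of three to four. On the interval reading the maximum does nothing in this step.
- The high-Hb step lowers the dose, so its counterpart would be expected to raise it.
- The condition that iron indices be on target first fits an increase.

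For the interval reading:

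- The sentence speaks of a single dose.
- In the same section and under Control group, a similar two-week phrase denotes plain spacing, for Hb checks and for iron sucrose.
- A maximum limits only the top and does not rule out a lower dose.

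**The case against.** The strongest reply is that a clinician would not read the step backwards. Taken as a whole the section points to an increase, and the interval reading makes the rule contradict its own purpose. That stands as a reason to think the period reading was intended. It does not make the sentence clear, because the interval reading remains a literal one and nothing in the article excludes it.

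Three further points also stand.

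- The article condenses a separate protocol (version 1.1, cited under Trial design and Trial status) that is not shown. Sites may work from clearer text.
- The rule is identical in both arms, so the ambiguity by itself favours neither.
- Leaving the investigator to choose between a minimum and a stated maximum is a design choice, not an error.

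A reader might infer that sites will deliver a three-fold range of doses, or that the direction of the cost comparison hangs on how sites read the sentence. The documents do not support either. They permit a spread but do not show that any site adopts the lower reading, and they give no figure for low-Hb time by arm. A reader might also expect under-dosing to drive participants toward the exit limit of Hb below 90 g/L. That is conceivable on the interval reading, but nothing in the article quantifies it.

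**Conclusion.** The point holds as a defect in a stated rule, not as an omission. The low-Hb epoetin step admits 5,000 U/week or 15,000 to 20,000 U/week, a three- to four-fold difference in rate that applies only while Hb is below 110 g/L with TSAT and SF on target. The 24-week totals of 210,000 U against 270,000 to 300,000 U rest on an assumed single 6-week episode with maintenance dosing otherwise; more or longer episodes would widen the gap, and none would remove it.

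The consequence is possible between-site variation in the drug-cost and Hb secondary endpoints. The comparison between arms would be biased only if time with low Hb, or the interpretation of the rule, differed by arm. Either is possible in an open-label trial, but neither is shown. It would go too far to say that the primary endpoint, TSAT at week 12, is compromised. Correction is worthwhile because it is cheap and because the rule governs dosing in participants with low Hb.

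**What to change.** The sponsor's clinicians should reconcile the low-Hb sentence with the stated maintenance dose, the restart rule after high Hb and the stated maximum. The revised text should say whether the two weeks are the dosing interval or the counting period. The same wording should go to all 9 sites. No dose or titration rule is proposed here.

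If the full protocol is already unambiguous, it is enough to confirm this and align the published text. Otherwise the cost is one amended sentence and a site memo, with no added visits, procedures or participants.
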